### Study design

We will use a randomized, non-concurrent, multiple baseline design across participants to investigate the efficacy of our game-based intervention to improve SVMC. The study will consist of a baseline phase of random length, i.e., 5 to 8 short assessment sessions distributed over 5 to 10 weekdays. The assessment sessions will include the measurement of the primary outcome (a short game-based SVMC assessment) and dynamometry of the target muscle group. During the intervention phase, participants will receive 10 treatment sessions of 40 min of our game-based SVMC training during 10 to 13 weekdays, while the short assessment will be continued (Fig. 1). Participants will train selective control of one individually determined target movement or muscle group, while trying to reduce the occurrence of involuntary movements or muscle activations around another predefined joint. Further assessments (see outcome measures) will be conducted at the beginning of the baseline phase, at the transition from the baseline to the intervention phase, at the end of the intervention phase, and at a follow-up 12 weeks after completion of the intervention.

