**Fig. 1 Fig1:**
[figure not shown]
Flow diagram of the study. The baseline phase will encompass randomly between 5 to 8 assessment sessions. Comprehensive outcome measurements will be conducted during the first and last appointment. For the other occasions, only a short assessment of selective control, muscle strength and motor control of the joint showing involuntary co-movements or co-activations is planned. During the intervention phase, participants will receive 10 sessions of game-based SVMC training. The short assessments (only SVMC and strength) will be continued after each treatment session, and the full assessment battery will be repeated at the end of the intervention as well as 12 weeks after completion. The study will run concurrently to the participant’s individual rehabilitation at the Swiss Children’s Rehab. Abbreviations: SVMC: selective voluntary motor control, SVMC mini-assessment: short game-based assessment to repeatedly measure selective control, SCALE: selective control assessment of the lower extremity, SCUES: selective control of the upper extremity scale, TMS: transcranial magnetic stimulation, MMT: manual muscle test, MAS: modified Ashworth scale, HAT: Hypertonia Assessment Tool

The study will run concurrently to intensive multimodal rehabilitation at the Swiss Children’s Rehab, which can consist of physical-, occupational- or speech and language therapy, sports therapy including endurance or strength training or sports groups, and/or robotics arranged according to the individual needs of the patient. A given number of assessment time points but variable time periods for each phase allow some flexibility to fit the children’s schedules.

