### Statistics

#### Primary research aim

The statistical analyses will be carried out with R statistical package [38]. The primary analysis of the efficacy will include a (hierarchical) mixed-effect model for the variable combining the accuracy and involuntary movement outcome. On a first level, the scores of the individual participant will be modeled by a set of predefined predictors, i.e., the session number (time), and the interaction of the session with the treatment phase. On a second level, the model parameter estimates will be allowed to vary between participants (random effects). We will account for the serial dependency of the data with a first-order autoregressive correlation structure of within-subject errors. The parameter of primary interest will be the interaction of time with the treatment phase, hence the change in trend when the intervention is introduced. Depending on the distribution and shape of the trend of the data, linear or additive mixed models will be used. Additionally, the same analysis will be conducted for the accuracy and involuntary movement outcome separately to investigate whether they show comparable effects.

For a patient-level analysis, a similar regression model will also be run for each individual participant.

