#### Secondary research aims

We will extend the primary model to analyze whether there exist interactions between the main parameter of interest (interaction of session with treatment phase) and secondary or descriptive outcomes. These other predictors encompass participant characteristics, active training time, muscle strength, and clinical SVMC measures of the target joint at baseline. Changes in muscle strength will also be analyzed with a mixed-model with the same parameters described above for the primary outcome.

We will calculate Kaplan-Meier curves that model the estimated probability of nonresponse by the number of intervention sessions and determine the median time to response (smallest number of sessions at which the probability drops to 0.5 or below). The criterion for response will be an improvement by 10% compared to the baseline level in the game-based mini-assessment of SVMC, represented by two consecutive data points in the intervention phase exceeding this threshold. As studies about meaningful changes in SVMC are not available yet, we estimated the response threshold via the standard error of measurement of several assessments of SVMC. One standard error of measurement corresponds roughly to changes of 10%.

For clinical SVMC measures, cortical excitability, and functional independence, changes during the baseline and intervention phase will be compared using paired t-tests or robust alternatives. We will account for the variable length of these phases by analyzing changes relative to the length of the corresponding phase. The length of each phase will be defined as the number of therapy days in between the first and last mini-assessment of each phase. The days of the first or last assessments themselves will also be counted if the first session was in the morning or if the last session was in the afternoon. We will test in the same way for differences in the frequency of other therapies participants attended between baseline and intervention phase. To analyze changes in the accuracy of motor control of the joint/muscle that will be trained to remain inactive, we will check whether the post-intervention score lies within the 95% prediction interval of the baseline scores.

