A limitation of the current study design is that it only investigates the effect of additionally providing our game-based SVMC training to regular rehabilitation but does not allow to compare the intervention to an equally dosed alternative treatment. However, this design was chosen because it will be the first time an SVMC training that targets both accurate movement control and a reduction of involuntary movements is investigated, and thus, this study can provide a first proof of principle. Moreover, the game-based SVMC intervention will only make up a small part of the therapy program the participant will receive during the study period. The intensive rehabilitation program running in the background of the study could affect the treatment effects. We might only see small differences between the baseline and the intervention phase because the regular rehabilitation program is included in both phases. However, we assume we will be able to see treatment effects because we focus very specifically on SVMC, and improving SVMC is rarely a therapeutic goal in other therapies [46]. Furthermore, we provide the intervention with a high frequency, i.e., the treatment sessions will be distributed over a short period. Apart from the frequency, the total dosage is comparable to the protocols of the few studies that aimed at improving aspects of SVMC so far, which applied training intensities between 4 and 9 h of treatment over 5 or 6 weeks [14, 15, 47, 48]. We account for the effects of the concomitant therapies as well as for spontaneous recovery in patients with subacute acquired brain injuries by comparing the trend of changes between the baseline and intervention phase or the changes relative to the length of the phases. Besides analyses on the group level, we will also look at each participant individually to address the heterogeneity of the study population.

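### With session number as the time axis, uneven weekday spacing between phases can turn a steady daily recovery trend into an apparent change in trend; expected group bias is modest, single-child distortion can be large

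*Protocol article*

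**What the plan says.** Under Statistics, Primary research aim, each child's scores are modelled by "the session number (time), and the interaction of the session with the treatment phase". The estimand follows: "The parameter of primary interest will be the interaction of time with the treatment phase, hence the change in trend when the intervention is introduced". The same section plans a similar regression for each child.

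Under Study design, the baseline phase has "5 to 8 short assessment sessions distributed over 5 to 10 weekdays". In the intervention phase, "participants will receive 10 treatment sessions of 40 min of our game-based SVMC training during 10 to 13 weekdays". The text below Fig. 1 makes the looseness deliberate: "A given number of assessment time points but variable time periods for each phase allow some flexibility".

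Under Secondary research aims, a correction for days is given for clinical SVMC measures, cortical excitability and functional independence: "We will account for the variable length of these phases by analyzing changes relative to the length of the corresponding phase". Phase length is defined there in therapy days. The muscle-strength model takes the same parameters as the primary model, and individual strength and SVMC interaction coefficients are later correlated. Neither the primary model nor the strength model has a day or phase-length term.

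The Discussion says that concomitant therapies and spontaneous recovery are accounted for by "comparing the trend of changes between the baseline and intervention phase" or by scaling changes to phase length.

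**The concern.** Regular rehabilitation and spontaneous recovery run through both phases and plausibly accrue per day. On a session axis, a constant daily rate becomes a slope of rate × weekdays per session. If that spacing differs between phases, the slope changes at the phase boundary although nothing in the child's recovery has changed, and the primary parameter picks this up.

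The direction depends on the schedule. A stretched baseline makes improvement before treatment look steep per session and hides benefit. A stretched intervention phase or a compressed baseline does the opposite. At stake are the interpretation of the primary interaction as a treatment effect and, more sharply, the results for individual children.

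**Working it through.** The plan gives no figure for this quantity. Its sample size does not use the time scale and is reproduced without it: 78.4 × 3.79 / 16.5 = 18.0, and 18.0 / 0.9 = 20.

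**Inputs from Study design.** Baseline: 5 to 8 sessions over 5 to 10 weekdays. Intervention: 10 sessions over 10 to 13 weekdays.

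**Assumptions, not in the document.** Background improvement of 1 point per weekday (results scale linearly), no treatment effect, evenly spaced sessions within a phase.

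**Step 1, spacing.** Weekdays per interval = (weekdays − 1) / (sessions − 1).
- Baseline extremes: 4/7 = 0.57 (8 sessions in 5 weekdays) and 9/4 = 2.25 (5 in 10).
- Intervention extremes: 9/9 = 1.00 and 12/9 = 1.33.

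**Step 2, spurious slope change for one child.** With separate slopes per phase: daily rate × (intervention spacing − baseline spacing). Noiseless fits give the same values. The last column fits only the two quoted terms, with no phase intercept.

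| Baseline, then intervention (sessions in weekdays) | Spacing difference | Spurious change per session | Without phase intercept |
|---|---|---|---|
| 5 in 10, then 10 in 10 | 1.00 − 2.25 | 1.25, hides benefit | 0.20, hides benefit |
| 6 in 8, then 10 in 10 | 1.00 − 1.40 | 0.40, hides benefit | 0.08, hides benefit |
| 8 in 8, then 10 in 13 | 1.33 − 1.00 | 0.33, favours training | 0.05, favours training |
| 8 in 5, then 10 in 13 | 1.33 − 0.57 | 0.76, favours training | about 0.16, favours training |
| 5 in 5, then 10 in 10 | 1.00 − 1.00 | 0 | 0 |

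With weekday as time, every row is 0.

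**Step 3, expected group bias.** Take baseline lengths 5, 6, 7 and 8 as equally likely, weekdays uniform over the allowed range, and at most one session per day.
- Mean baseline spacing by length: 1.625, 1.400, 1.250, 1.143; overall 5.418 / 4 = 1.35.
- Mean intervention spacing: 10.5/9 = 1.17.
- Difference: 0.19 points per session toward hiding benefit. At 0.5 or 2 points per weekday it is about 0.09 or 0.38.

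**Step 4, size against noise.** Assume residual SD 10, independent errors, no between-child slope variance, 20 children. The variance of one slope difference is 100 × (1/Sxx,baseline + 1/Sxx,intervention), with Sxx = n(n² − 1)/12. For n = 5, 6, 7, 8, Sxx = 10, 17.5, 28, 42, so the mean of 1/Sxx is 0.0542. For n = 10, 1/82.5 = 0.0121. The standard error is √(100 × 0.0663 / 20) = 0.58, so the bias is 0.19 / 0.58 ≈ 0.3 standard errors.

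**Step 5, simulation under no treatment effect.** 20 children, residual SD 10, AR(1) 0.2, 600 runs, nominal 5% (simulation standard error about 0.9 percentage points), slopes of 0.5, 1 and 2 points per weekday.
- Session axis, weekdays drawn uniformly, slope-change codings: about 4–7% rejection.
- Session axis, every baseline spread over 10 weekdays and intervention 10 in 10, slope-change codings: about 7–8%, 18–19% and 48–53%.
- Session axis, same spread schedule, quoted terms without phase intercept: at most 12%.
- Day axis: about 4–7% throughout.

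**The case against.** Much of the case on the other side stands.

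- A reader might infer from the first row of the table that the whole trial could be biased by 1.25 points per session. That needs every child to have five baseline sessions. The plan randomises 5 to 8 with an urn scheme that favours balance, and its sample size expects 16.5 points per child, that is 6.5 in baseline. Expressing that case in standard errors (1.25 / 0.75 ≈ 1.7 at SD 10) also needs a residual SD that the document does not give.
- Midpoint spacings almost coincide: 6.5/5.5 = 1.18 in baseline and 10.5/9 = 1.17 in the intervention phase.
- The lower limits, 5 sessions in 5 weekdays and 10 in 10, suggest at most one session per day. If so, the 8-in-5 schedule does not arise and the largest difference favouring the training is 0.33. The text does not state that limit.
- The listed predictors contain no phase intercept. Read literally, the bias is much smaller.
- One point per weekday may be too fast, since the Discussion says SVMC is rarely a goal of other therapies.
- Session number is a defensible axis. Training comes per session, and the plan itself expects initial learning on the test. If practice accrues at 1 point per session, the day axis creates the mirror artefact: for 5 in 10 then 10 in 10, 1/1.00 − 1/2.25 = 0.56 points per day.
- The secondary outcomes are mainly changes between phase ends and need a length divisor, so the contrast with the primary model shows less than it might seem to.
- A reader might also infer that the autoregressive errors ignore unequal gaps. The plan does not say on what index they are defined.

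These points limit the size. They do not remove the mechanism: nothing in the plan requires equal spacing, and averaging over children does not repair individual results.

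**Conclusion.** The concern holds in a limited form. The session axis is a stated choice, spacing may differ between phases, and a constant daily trend then leaks into the primary interaction. The Discussion's claim to account for recovery and concomitant therapy is therefore conditional on equal spacing.

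The expected group effect is modest and tends to hide benefit; with weekdays drawn uniformly, the false-positive rate stays close to nominal. It becomes material only if scheduling is systematically lopsided and background recovery is fast. The document does not support calling the primary test invalid.

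The patient-level consequences are stronger: up to 1.25 points per session at the assumed rate, 0.63 at half that rate. The correlation of strength and SVMC coefficients is particularly exposed. Both coefficients of a child come from one schedule, so if both outcomes drift daily, scheduling alone can induce an association.

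All sizes rest on the assumed daily rate, and those in standard errors or rejection rates also on the assumed residual SD. This should be settled before analysis; it does not require a change of design.

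**What to change.** Prespecify a second model with elapsed weekdays since the first baseline assessment as time, or the therapy days already defined under Secondary research aims. Measure the slope change in time since the first intervention session, state whether a phase intercept is included, and use a serial correlation that allows unequal gaps, such as a continuous-time AR(1).

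Report it beside the session-number model, which captures practice effects that accrue per session. Claim control of spontaneous recovery and concomitant therapy only if the two agree, and reword the Discussion accordingly. Apply the same pair of models to the patient-level regressions, the strength model and the coefficient correlation, and tabulate each child's weekdays per session by phase.

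The cost is analysis wording plus the date of each session; the phase-length definition already needs the first and last of these. The sample size stays at 20. The downside is that the day scale misattributes per-session practice, which is why neither model should stand alone.

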#### Secondary research aims

We will extend the primary model to analyze whether there exist interactions between the main parameter of interest (interaction of session with treatment phase) and secondary or descriptive outcomes. These other predictors encompass participant characteristics, active training time, muscle strength, and clinical SVMC measures of the target joint at baseline. Changes in muscle strength will also be analyzed with a mixed-model with the same parameters described above for the primary outcome.

We will calculate Kaplan-Meier curves that model the estimated probability of nonresponse by the number of intervention sessions and determine the median time to response (smallest number of sessions at which the probability drops to 0.5 or below). The criterion for response will be an improvement by 10% compared to the baseline level in the game-based mini-assessment of SVMC, represented by two consecutive data points in the intervention phase exceeding this threshold. As studies about meaningful changes in SVMC are not available yet, we estimated the response threshold via the standard error of measurement of several assessments of SVMC. One standard error of measurement corresponds roughly to changes of 10%.

For clinical SVMC measures, cortical excitability, and functional independence, changes during the baseline and intervention phase will be compared using paired t-tests or robust alternatives. We will account for the variable length of these phases by analyzing changes relative to the length of the corresponding phase. The length of each phase will be defined as the number of therapy days in between the first and last mini-assessment of each phase. The days of the first or last assessments themselves will also be counted if the first session was in the morning or if the last session was in the afternoon. We will test in the same way for differences in the frequency of other therapies participants attended between baseline and intervention phase. To analyze changes in the accuracy of motor control of the joint/muscle that will be trained to remain inactive, we will check whether the post-intervention score lies within the 95% prediction interval of the baseline scores.

To analyze the association of changes in SVMC and muscle strength, we will correlate the regression coefficients for the interaction of the session and treatment phase from the strength and the SVMC model of each individual participant. For TMS outcomes, we will further correlate pre- to post-intervention differences with changes in SVMC measures. Follow-up data will be analyzed by paired comparisons (t-test or robust alternative) between post-intervention and follow-up assessments (to test whether the level is maintained) and between the measurement directly before the intervention and at follow-up (to test whether the level is still higher than before starting the intervention).

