#### Cortical excitability

We will use a standardized protocol to determine the motor threshold and the latency and amplitude of the motor evoked potential (MEP). A single-pulse TMS will be performed using a MagPro X100 Magnetic Stimulator (MagVenture A/S, Farum, Denmark) in combination with a Keypoint G3 Workstation (DANTEC Medical A/S, Skovlunde, Denmark). Electrodes will be placed on the muscle belly of the muscle that is also the target muscle group of the intervention. For all measurements, a MFC-B65 Butterfly figure-of-eight coil will be used to stimulate the primary motor cortex. If a lower extremity muscle group is trained, the coil will be positioned just lateral to the midline, close to Cz (Vertex), contralateral to the target muscle [32]. If an upper limb muscle group is trained, the coil will be positioned close to C3h (left) or C4h (right) [33]. The coil will be moved in small increments to find the location with the largest response (i.e., hot spot). Participants will wear a bathing cap and this location will be marked on it. We will use a biphasic single-pulse stimulus, as these are more effective than monophasic pulses, with a pulse duration of 200 μs. The stimulus threshold will be expressed as the percentage of maximal stimulator output that evokes an MEP amplitude of at least 50 μV in approximately 50% of 10 consecutive stimuli (i.e., motor threshold). The stimulation intensity will be set at 1.2 times the motor threshold. We will perform five stimulation repetitions to determine the parameters latency and amplitude of the MEP in the averaged signal. On the second and third TMS test occasions, the procedure will be repeated. Again the stimulation threshold is determined and noted for comparison. Independent from the new threshold level, the stimulations to determine MEP latency and amplitude are performed at the same level of stimulator output as performed during the first measurement. TMS measurements will be conducted in separate appointments.

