#### Functional independence

To assess the children’s functional independence in daily life activities, we will use the domains mobility (for the lower extremities) and self-care (for the upper extremities, excluding bladder and bowel items) of the Functional Independence Measure for children (WeeFIM®). The WeeFIM® measures activity on the performance level and rates independence on a scale from 1 (total assistance needed) to 7 (complete independence, performs task timely and safely) [34]. In the Swiss Children’s Rehab, it is assessed by trained and certified nurses on a regular basis.

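### For SCALE/SCUES, the intervention-phase change starts at the transition assessment, but the day count that divides it starts only at the mini-assessment after training session 1

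*Protocol article*

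**What the plan says.** All references are to the protocol article.

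- **Rate analysed.** Under Secondary research aims, changes in clinical SVMC measures, cortical excitability and functional independence are compared between phases with paired tests (a t-test or a robust counterpart), on this scale: "We will account for the variable length of these phases by analyzing changes relative to the length of the corresponding phase".
- **Denominator.** "The length of each phase will be defined as the number of therapy days in between the first and last mini-assessment of each phase". A half-day rule follows: "The days of the first or last assessments themselves will also be counted if the first session was in the morning", and likewise for the last day if the last session was in the afternoon.
- **When the full battery is taken.** For the baseline phase, the Fig. 1 legend says "Comprehensive outcome measurements will be conducted during the first and last appointment". Study design places the later batteries "at the transition from the baseline to the intervention phase, at the end of the intervention phase", and then at the 12-week follow-up. No full battery is described at the first training session.
- **When the intervention mini-assessments are taken.** Fig. 1 legend: "The short assessments (only SVMC and strength) will be continued after each treatment session". Primary outcome also places the test immediately after training, and Sample size calculation counts 10 of them, one per session.
- **Other outcomes.** Cortical excitability: "TMS measurements will be conducted in separate appointments". For WeeFIM, Functional independence says "it is assessed by trained and certified nurses on a regular basis".

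**The concern.** A rate is interpretable only if its change and its time span cover the same interval. In the baseline phase they do for SCALE/SCUES. In the intervention phase the change begins at the transition appointment, but the clock starts only after session 1 has been delivered.

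The Discussion relies on analysing changes relative to phase length as one of its two ways of allowing for concomitant therapy and spontaneous recovery. For these paired comparisons it is the only one. If a child recovers at the same daily pace in both phases and training adds nothing, the two rates should be equal. A denominator that is too short in one phase makes that phase look faster. Here it is the intervention phase, in children who are receiving intensive rehabilitation throughout, some of them with subacute injuries.

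**Working it through.** The protocol gives no figure for phase length or for the gap between phases, so there is no stated result to reproduce. The check applies its counting rule to both spans.

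**Inputs from the protocol article**
- Intervention phase: 10 sessions over 10 to 13 weekdays (Study design).
- Counting rule: therapy days strictly between two sessions, plus the first day if that session is in the morning, plus the last day if that session is in the afternoon (Secondary research aims).

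**Assumptions**
- Gap g is the number of therapy days from the last baseline appointment to session 1, where 1 means the next therapy day. It is not stated; 0, 1 and 2 were tried.
- Each weekday of the phase is a therapy day.
- The end-of-intervention SCALE/SCUES is taken at the same appointment as the last mini-assessment.
- Background change per therapy day is constant and training has no effect.

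**Formulae**, for a phase of N days
- Denominator as written: A = (N − 2) + [session 1 in the morning] + [last session in the afternoon].
- Days the change covers, for g of 1 or 2: B = (g + N − 2) + [last baseline visit in the morning] + [last session in the afternoon].
- Each bracket is 1 if true and 0 if not. Inflation of the intervention rate is B/A − 1.

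**Results for N = 10, g = 1**

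| Last baseline visit | Session 1 | Last session | A | B | B/A |
|---|---|---|---|---|---|
| afternoon | morning | morning | 9 | 9 | 1.000 |
| afternoon | morning | afternoon | 10 | 10 | 1.000 |
| morning | morning | afternoon | 10 | 11 | 1.100 |
| morning | morning | morning | 9 | 10 | 1.111 |
| afternoon | afternoon | afternoon | 9 | 10 | 1.111 |
| afternoon | afternoon | morning | 8 | 9 | 1.125 |
| morning | afternoon | afternoon | 9 | 11 | 1.222 |
| morning | afternoon | morning | 8 | 10 | 1.250 |

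**Range over all session times**

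| Assumed gap | 10 weekdays | 13 weekdays |
|---|---|---|
| 0 (baseline visit in the morning, session 1 the same afternoon) | 11-13% | 8-9% |
| 1 therapy day | 0-25% (unweighted mean 11%) | 0-18% (unweighted mean 9%) |
| 2 therapy days | 10-38% | 8-27% |

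For example, N = 13 and g = 1 gives at most 13/11 = 1.18. N = 10 and g = 2 gives at most 11/8 = 1.375.

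For SCALE/SCUES in the baseline phase, both spans run from the first to the last baseline appointment, so the ratio is 1.00. The intervention ratio was never below 1 in any combination.

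**Effect on the test, as an illustration.** Take a paired t-test with n = 20, two-sided 5%, and let δ be the background rate in units of the SD of the paired rate difference (assumed values). The noncentrality is inflation × δ × √20.

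| Inflation | δ = 0.2 | δ = 0.5 | δ = 1 |
|---|---|---|---|
| 10% | 5.1% | 5.5% | 7.1% |
| 25% | 5.5% | 8.3% | 18.6% |

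The entries are false-positive rates.

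**The case against.** Five points can be made on the other side.

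- **The half-day rule already corrects for this.** It does so in part. When session 1 is in the morning, its whole day is counted, so it would be wrong to say that session 1 is always left out. At a 1-day gap the error vanishes if the last baseline visit is in the afternoon and training starts the next therapy morning. In the other 1-day cases it remains, and at a 2-day gap it never falls to zero.
- **The gap is probably short.** The protocol speaks of an assessment at the transition, and its follow-up analysis refers to the measurement directly before the intervention. Weekends should not count as therapy days. This makes the lower figures more plausible, but no gap is fixed and the Fig. 1 text allows flexible scheduling.
- **The length definition serves a purpose.** It matches the window in which concomitant therapies are recorded (Potentially confounding ongoing therapies), so it is coherent for comparing therapy frequency. That stands, but it does not make the definition fit the outcome changes.
- **This is detail for an analysis plan.** The article states the rule explicitly; the problem is a stated rule that does not fit its numerator.
- **The consequence is small.** It often is: with 10% inflation and modest background change, the test is barely affected.

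A reader might infer that every secondary comparison is biased towards the intervention. The documents do not support that. TMS has its own appointments and WeeFIM follows the nurses' schedule, so their intervals may differ from the mini-assessment dates in either phase, and the direction of the error is unknown.

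**Conclusion.** The mismatch is real for SCALE/SCUES and follows from the current text. Its size is conditional on a gap that the protocol does not state: 0-25% (10 weekdays) or 0-18% (13 weekdays) at an assumed gap of 1 therapy day, and 10-38% or 8-27% at 2 days. These ranges also assume that the final SCALE/SCUES coincides with the last mini-assessment.

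The error multiplies whatever change is observed. It favours the intervention when there is steady background improvement, is nil when nothing changes, and magnifies a deterioration. It would therefore be too strong to say that the intervention rate is always inflated, or inflated by a fixed percentage.

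A reader might also infer that the main efficacy result is at risk. It is not: the primary mixed model uses session number, and neither that model nor the sample size uses this phase length. The strength mixed model, with the same parameters, is likewise unaffected. The point concerns the secondary paired comparisons only, and it should be corrected before analysis.

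**What to change.** For clinical SVMC measures, TMS and WeeFIM, divide each change by the therapy days between the two assessments that produce it, with the same half-day rule:

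- baseline phase: first to last baseline assessment of that outcome;
- intervention phase: transition assessment to end-of-intervention assessment of that outcome.

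Use the actual date and time of day of each assessment. Keep the mini-assessment-based length only for the comparison of concomitant-therapy frequency, where it matches the recording window.

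The cost is one changed definition and no extra visits. The small downside is that the actual dates of each outcome assessment must be available, as must the therapy days in the gap before session 1. The article does not say that these are kept, and the therapy record it describes covers only the span between the first and last mini-assessment of each phase.
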